## Abstract

Aim of this paper is to describe the protocol of the study “Impact of a Community-based Program on Prevention and Mitigation of Frailty in community-dwelling older adults” developed in the framework of the European Innovation Partnership on Active and Healthy Ageing. This proposal has been developed by the Partnership Action groups on frailty, fall prevention and polypharmacy in older. The proposal wants to assess the impact of community-based programs aimed to counteract three main outcomes related to frailty: hospitalization, institutionalization and death. Bringing together researchers from seven European countries, the proposal aims to achieve the critical mass and the geographical extension enough to provide information useful to all older European citizens. An observational study will be carried out to calculate the incidence of the different outcomes in relation to the various interventions that will be assessed; results will be compared with data coming from already established national, regional and local dataset using the observed/expected approach. The sample will be made up by at least 2000 citizens for each outcome. All the citizens will be assessed at the baseline with two multidimensional questionnaires: the RISC questionnaire and the Short Functional Geriatric Evaluation questionnaire. The outcomes will be assessed every six-twelve months

## Introduction

Frailty is a multidimensional syndrome predisposing to the development of functional decline in older adults [1, 2]. It is characterised by a loss of physiological reserve, often in the setting of limited socio-economic resources that results in increased vulnerability to adverse healthcare outcomes. It is also associated with the increased use of social and health care services. Comprehensive frailty assessment facilitates the planning of health and social care services, both at an individual and population level [3–6]. This approach is only now beginning to be adopted in public health [6 – 8]. Even if assessment of frailty is not yet a common step for accessing appropriate care pathways, some European Union (EU) countries have developed integrated models of frailty assessment and good practices to address the management of chronic diseases that have been implemented locally or regionally in several member states [9–14].

To be successful in managing the care of frail older adults with chronic diseases, interventions must link health and social care systems together with supportive living environments capable of fostering the patient through different stages of diseases and functionality [15, 16]. The EU Commission and the Economic Policy Committee state that although increases in longevity must be accompanied by an increase in the number of years spent in good health and improvements in the health of those less well-off, this represents a policy challenge with potential significant repercussions on future expenditure trends [17]. A new public health approach, able to offer appropriate care to frail older patients through the different stages and severity of disease states, is therefore required. A pro-active model centered on frailty assessment [9] could become an entry point for patients and healthcare professionals to access integrated care, while the integrated management of chronic disease and frailty prevention programs could offer appropriate tailored care pathways to each patient [18,19].

While there are growing data suggesting that community-based programs assessing frailty and implementing interventions to prevent or mitigate frailty are able to impact upon its incidence and progression [9, 20], few studies have brought together data from several sources and researchers from different settings to investigate the scalability of differing approaches across the EU. This is a missed opportunity to assess crucial information that may influence healthcare policy and direct future funding. Indeed, it could be argued that inequalities across European countries and within each country are deep.

To pool, synthesize and evaluate many of the ongoing EU frailty studies represents an opportunity to take advantage of these often well-conceived but seemingly disparate projects. This approach is highly relevant given the emphasis the EU has been placing on preventing onset of frailty and functional decline through the launch of the European Innovation Partnership on Active and Healthy Ageing (EIP-AHA) and in particular, its A3 Action Group (EIP - AHA, DG Santé and DG CONNECT) [21]. The A3 Action Plan focuses on innovative approaches to prevent and manage frailty that include the fundamental components of education, training and empowerment of professionals and citizens [22]. It is also coherent with proposed work of the recently funded Joint Action on Frailty called ADVANTAGE, which plans to outline a joint framework to tackle frailty by tailoring available good practices to specific loco regional settings, thus facilitating scalability and adoption.

This paper describes the collaborative work (“synergy”): Impact of Community-based Program on Frailty Prevention and Mitigation of Frailty (ICP – PMF), launched by A1, A3, and B3 partners of the EIP - AHA, to investigate if common approaches to mitigate frailty in community dwelling older adults can be scaled-up specifically to develop and implement a practical screening approach to allow early detection of frailty. Thus, under the framework of the EIP-AHA’s Task Force on Synergies, a consortium of stakeholders from several EU countries (Table 1), led by the Biomedicine and Prevention Department of the University of Rome “Tor Vergata”, will measure the impact of several ongoing community-based interventions on the prevention and/or mitigation of frailty in line with the Monitoring and Assessment Framework for the European Innovation Partnership (MAFEIP) [23, 24].

The ICP –PMF synergy proposes to develop a feasible, achievable and manageable project using existing networks and stakeholders committed to the A3 Action Plan of the EIP –AHA [21,22] i.e. those currently involved in ongoing commitments (funded and unfunded projects) of the EIP- AHA. (Table 2).

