### Sample

Subjects for inclusion/assessment will be aged over 64 years and living at home; those living in an institution (nursing homes or similar) will be excluded. Each study site can decide to restrict the field of intervention with additional exclusion criteria. The total number of European citizens involved in the assessment will be around 2000 for each outcome of which at least 20% will be enrolled before the end of June 2016.

Participants will be enrolled among the ones who access the services managed by the stakeholders involved in the proposal. In Ireland, participation in the study will be offered to community-dwelling older adults who are under surveillance by their Public Health Nurse consistent with ongoing studies in this setting [10, 13, 14]; in Valencia participant will be the women who access the outpatients department of the University Hospital gynecologic service for health control. In Genoa participants to the DOREMI project will be enrolled enrolled involving citizens who access to the local University Hospital. In Barcelona participants will be enrolled among communitydwelling older adults who are attended by their primary health care team, both in the office and at home. In Twente and Campania, community dwelling older adults will be enrolled among participants to the PERSSILAA project, patients referring to Federico II outpatients practices and to the GPs of the Salute in Collina no profit organization. Campania study sample will also include participant to the Sunfrail pilot, and to the Beyond Silos project in Salerno. In Rome the over-74 citizens reached by the Viva gli Anziani program (all living in the community) will be included in the study. In Porto participants will be primary care patients of Health Centers that agreed to participate. People over 64 years will be prescreened by trained GPs and further assessed by the CARTS project team, supported by the General Directorate of Health. In Parma the over 64 citizens of Central District of Parma will be included as part of Sunfrail and SprinTT recruitment process. In Pecs community dwelling older adults will be enrolled from members and clients of local NGO’s Wherever possible the General Practitioner of the citizens involved in the study will be informed.

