### Baseline assessment

The baseline assessment aims to stratify the population, (from robust to frail individuals) according to the risk on negative outcomes. The basis of the stratification is the operative definition of frailty above-mentioned.

The tool to be used should:

Identify frail individuals and size the risk of hospitalization, institutionalization and death as well as the trend of this risk during the follow up according to the exposure to interventions to cope with frailtyCover the five domains of frailty: social and economic resources, functional status, physical and mental health;Be short and easy to administer in order to involve thousands of citizens;Be simple in order to involve non –health professional personnel, such as the care-giver to administer it.

The working group reached a consensus on two common instruments for baseline assessment:

The **Risk Instrument for Screening in the Community** can be used to quickly screen large numbers of patients to identify and stratify those at greatest risk of three adverse healthcare outcomes (institutionalisation, hospitalisation and death) [10, 13, 37–41]. These patients can then be triaged for further assessment, investigation and treatment with integrated care bundles or other management strategies that are location or service specific. The RISC tool collects demographics, records concerns, the severity and ability of the caregiver network to manage three main domains (mental state, ADL state and medical state issues). It then summarises the perceived risk using a subjective, global score of risk based upon a five-point Likert scale measured from 1 (minimal-rare risk) to 5 (extreme-certain). The RISC was developed as an exemplar under the EIP on AHA reference site COLLAGE, Ireland’s only reference site for active and healthy ageing. It has been translated into multiple languages (English, Dutch, Italian, Spanish and Portuguese). It has been validated in multiple sites in the EU as part of work conducted in Action Group A3 of the EIP on AHA including in Porto (34) and Barcelona. The RISC stratifies risk of adverse healthcare outcomes by measuring the magnitude of functional, physical or state mental concern.

Sometimes although the concern may be minimal, the lack of formal and/or informal caregivers may elevate or even multiple that risk.

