Salerno	Over 64 (100 ind.s)	two arms prospective observational	-SFGE -RISC	-Multidimensional assessment -Social and Health care integration -Electronic Clinical Record filled by the personnel and by the patient/caregiver -Home care monitoring and treatment by remote -Clinical management	Incidence of hospitalization Incidence of institutionalization Incidence of deaths	Control group
Twente	65–75 (300 ind.s)	two arms prospective observational	-GFI -SF-12 -SF-36 -MNA -SFGE -QMCI -NMA -Phys. test^6^	-frailty screening through multidimensional assessment -The PERSSILAA physical module Web-based exercising Monitoring	Incidence of frailty/functional decline Quality of LIfe	Control group
Valencia	Over 64 (1600 women)	Prospective observational	- Fried - CFS - SFGE - RISC	-Clinical assessments -Analytical Lab assessments -Bone metabolism assessment -Frailty assessment. -Cognitive frailty -Quality of life -Lifestyle intervention	Incidence of frailty Progression of frailty Incidence of hospitalization Incidence of institutionalization Incidence of death	pre and post-intervention assessment comparison with other cohorts within the working group (Twente)

**Table 4 t4-tm-15-53:** SPRINTS forecasted by the synergy proposal

N∘	Name	Starting date	Delivery date	Geographic coverage	Results
**S 1**	Set up a community - based public health approach to scale-up multidimensional screening tools in order to prevent, detect and manage frailty in community dwelling elderly. Target population and procedure to deliver the screening will be agreed. Ongoing interventions will be included into a common pathway defined by the assessment methodology.	15-Jan-2016	31-Mar-2016	Six Countries	Report on the action plan to implement a public health approach to frailty in community dwelling elderly and on the assessment methodology

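### Where people already in a running programme are enrolled, the study baseline can fall after exposure began, so change outcomes can miss effect already achieved and event rates come from those still at home

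*Protocol article*

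**What the plan says.** The Introduction says that the consortium "will measure the impact of several ongoing community-based interventions on the prevention and/or mitigation of frailty". Table 4, sprint S1, adds: "Ongoing interventions will be included into a common pathway defined by the assessment methodology".

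Under Sample, the general enrolment rule is: "Participants will be enrolled among the ones who access the services managed by the stakeholders involved in the proposal". It carries no condition that the person be new to the service. Three site descriptions matter here:

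- Rome: "In Rome the over-74 citizens reached by the Viva gli Anziani program (all living in the community) will be included in the study".
- Twente and Campania: community-dwelling older adults "will be enrolled among participants to the PERSSILAA project", along with outpatients, patients of certain general practitioners and (in Campania) participants of two further projects.
- Genoa: DOREMI project participants, recruited through the local university hospital.

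The same section sets the entry state: "Subjects for inclusion/assessment will be aged over 64 years and living at home". Residents of institutions are excluded.

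Time zero is defined by the study. Data collection has every site do a baseline assessment with the instruments chosen in the preparation phase. Follow up counts information obtained after that assessment. Table 4, sprint S2, counts 12 and 24 months of observation. The section on Baseline assessment requires the tool to size risk and also "the trend of this risk during the follow up according to the exposure to interventions".

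**The concern.** A baseline is a pre-intervention measure only if it is taken at or before first exposure. For someone already on a programme, it is an on-treatment measure. Two things follow.

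First, an improvement made before baseline is built into the baseline score. A change measured from there shows only what happens afterwards, so the programme can look less effective on incidence of frailty and on progression or regression of risk than it was.

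Second, anyone who died or entered an institution while on the programme before baseline cannot enter the study. Observed event rates then describe those who remained alive and at home, not everyone who started.

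Mixing such people with new entrants gives a pooled estimate that answers neither question cleanly. The expected reductions under Sample size are small (2.5% and 5%), so a modest distortion could matter.

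**Working it through.** No figure in the article measures prior exposure, so the check sets the rules side by side.

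1. **Exposure start.** The Introduction and Table 4 (S1) describe the interventions as ongoing. That describes programmes, not persons. The person-level evidence is in Sample: Rome enrols people the programme has reached, Twente/Campania draws partly on project participants, and Genoa on DOREMI participants.

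2. **Time zero.** Data collection and Follow up place it at the study's baseline assessment. Table 4 dates the methodology sprint 15 January to 31 March 2016 and the first risk classification 1 April to 30 June 2016. Nothing stated ties this date to a person's first contact with the programme.

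3. **Entry state.** Participants must be living at home at inclusion.

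4. **Comparator.** Study design matches the reference population on age, sex and location of residence, not on time in a programme.

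Taken together, a person can enter after exposure began, provided they are still alive and at home.

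**Which outcomes are touched where (Table 3).**

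| Site | Frailty-change outcome | Event outcomes |
|---|---|---|
| Rome | none | hospitalization, institutionalization, death |
| Naples (Campania) | incidence, progression | same three |
| Salerno (Campania) | none | same three |
| Twente | incidence of frailty/functional decline | none |
| Genoa | progression | same three |

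Rome, the clearest case of prior exposure, lists event outcomes only. Masking of change is therefore a question for Naples, Twente and Genoa. Rome faces the survivor question.

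**Illustration under assumptions (none of these inputs is in the article).**

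*Change outcomes.* Suppose an effect on frailty level builds up with half-life h years. The share already inside a baseline taken t years after first contact is 1 − 2^(−t/h).

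- t = 1: h = 2 gives 1 − 2^(−0.5) = 29%; h = 0.5 gives 1 − 2^(−2) = 75%.
- t = 2: h = 2 gives 1 − 2^(−1) = 50%; h = 0.5 gives 1 − 2^(−4) = 94%.

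*Event outcomes.* Let individual risk follow a gamma distribution with mean 1 and variance θ, and let H be the yearly hazard of death or institutionalization times the years before baseline. Mean risk among those still at home is 1/(1 + θH). With a true hazard ratio of 0.80, against a reference depleted over the same period, the ratio seen after baseline is 0.80 × (1 + θH)/(1 + 0.80θH).

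- θ = 0.5, H = 0.05 × 3 = 0.15: mean risk 1/1.075 = 0.93; ratio 0.80 × 1.075/1.06 = 0.81.
- θ = 2, H = 0.10 × 3 = 0.30: mean risk 1/1.6 = 0.63; ratio 0.80 × 1.6/1.48 = 0.87.

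Under these assumptions, change outcomes can lose a large part of the effect, while a continuing effect on events is weakened but still visible. The ranges show what prior exposure could do; they do not estimate what it does here.

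**The case against.** The strongest reply is that prior exposure is permitted by the text but not shown for any individual. In Rome, being reached may mean being contacted for the proactive screening that heads the site's list of activities. Genoa and Twente may assess people as they join the project. Genoa (about 30 people) is also listed as a pilot randomised trial, and Twente and Salerno have control groups. Barcelona lists a before-after interrupted time series and Valencia a pre/post-intervention assessment, both of which imply a measure before the intervention. All of this stands, and it limits the point to certain sites and to what can happen.

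It may also be said that a condensed article leaves time zero to a fuller document. That would answer a complaint about missing detail. Here, the enrolment, entry and follow-up rules that are stated produce the problem when followed as written.

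Three stronger readings are tempting and not supported:

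- *Uncounted early events bias event outcomes towards benefit.* The matched reference population has also survived to its age, and differential depletion alone pulls towards no effect, as shown above. Selecting people who stayed at home could flatter a programme, particularly if the reference includes institution residents, but that contrast arises for new entrants too. The net direction is open.
- *The loss of effect can be sized from a site's share of the Table 3 population.* Rome has no frailty-change outcome, and the 5% under Sample size is an expected reduction in event rates, not a change from baseline.
- *Ireland and Pecs are further examples.* Nurse surveillance and membership of a local organisation are recruitment sources. Neither is listed as the intervention under study.

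**Conclusion.** The point holds in a limited form. At sites that enrol people already reached by or taking part in a running programme (clearest in Rome, possibly Twente/Campania and Genoa), baseline and the start of follow-up can come after exposure began. Where that happens, frailty-change outcomes can miss effect already achieved, and event rates describe people who survived at home on the programme.

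Neither size nor net direction can be determined from the article, because it gives no proportion of existing users and no time already spent in a programme. The conclusion assumes that some enrolled people had earlier contact with the intervention being evaluated, which the enrolment wording allows but does not quantify. It does not extend to every site, and it does not make later event comparisons uninformative. The matter should be settled before effect estimates are pooled across sites.

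**What to change.** - Record, for each participant, the date of first contact with the site's programme.
- Present effect analyses separately for two groups. New entrants have their baseline assessment at or before first contact and events counted from that date. Existing users are reported by time since first contact.
- For change-from-baseline outcomes, give most weight to new entrants.
- Do not treat a score obtained on the programme as a pre-intervention baseline.

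The cost is one extra data field and lower precision in the new-entrant group, most of all at long-running sites, where that group may be small. For people already enrolled the date would have to be recovered from programme records; the article does not say whether these hold it, so sites should confirm this first.

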### Operational definition of frailty for the ICP – PMF synergy

At present, no standardised operational definition of frailty is accepted [25–27]. The international debate has focused on two main approaches to defining frailty: the first one addresses physical determinants (physical definition), while the second one takes into account cognitive, nutritional, psychological and socioeconomic factors (bio-psycho-social definition). For the purpose of this study the synergy consortium selected the latter definition given that that is the most commonly used by the partners, as well as the more appropriate in the framework a public health approach aimed at mitigating frailty [15, 28, 29].

In this sense, the operative definition of frailty relates to the risk of adverse healthcare outcomes (disability, hospitalisation, institutionalisation and death) to which the individual is exposed given the association between frailty level and risk: the higher the frailty level, the higher the risk [30, 31]. The incidence of these outcomes relates not only to the patient’s functional, physical or mental status but also to their socioeconomic status. Lacking social and/or economic resources leads to an increased use of acute care or long-term care services even if the individual has minimal functional impairment [32, 33].

It is well established that the risk of death is associated with social isolation and that a strong social network has a protective effect (34]. For these reasons, the role played by socio-economic resources in determining the incidence and prevalence of frailty needs consideration (see Figure 1).

## Objectives of the ICP –PMF Synergy proposal

### General Objectives

To set up a public health approach to prevent, identify and manage frailty in community dwelling older adults that can be validated in different EU member states.To identify factors that should be targeted in order to delay or postpone further decline and disability.

### Specific objectives

Emphasize the importance of comprehensive frailty assessment as good practice in the prevention and management of frailty by counteracting social isolation, improving nutrition, promoting adherence to therapy and encouraging physical activity.Promote the continuum of care by integrating social and health care at primary, secondary levels.Assess the impact of this public health model on the management of frailty in the community in terms of cost effectiveness, use of health services and acceptance by citizens.Test the relationship between a set of indicators and the prevalence of frailtyInvestigate the readiness for ICT supported managementDescribe the strengths and weaknesses of caregiver network’s, their role in the management of frailty, while implementing strategies to maintain, supplement and improve this network.

